#### Randomization, allocation concealment and blinding

Dutch consenting participants will be randomly allocated by the researcher to usual care (A) or dr. Bart (B) (allocation ratio 1:1) after completing baseline assessment performed with CastorEDC. CastorEDC uses a validated variable block randomization method (with randomly varying block sizes of 2, 4 and 6) and is stratified on the individual level by hip or knee OA. The researcher who will ascertain randomization will be concealed for treatment allocation. Due to the design of this study, blinding of participants and researchers is not possible. Data collectors will be blinded as data will be collected with validated questionnaires via CastorEDC. All German participants receive the dr. Bart app during the study (C), see Fig. 2.

#### Intervention (dr. Bart app)

Participants allocated to the Dutch dr. Bart group (B) and all German participants (C) will receive the dr. Bart app during the study.

#### Experimental intervention groups (arms B and C)

Participants allocated to the Dutch intervention group (B) and all German participants (C) will receive the dr. Bart app (version number 1.3.7) for 6 months. They can use the dr. Bart app “ad libitum”. The app is only accessible for users after the researcher has provided access for the app. Throughout the study, participants are able to call and send emails to the researcher when they have questions regarding the dr. Bart app or the study.

#### Usual care control group (arm A)

Half of the participants in the Netherlands will be allocated to the usual care group (arm A) and will receive no active treatment, but care as usual. Usual care is defined as de facto clinical care and will not interfere with usual care.

### Measurements

Three self-assessed sets of online questionnaires (at baseline and, 3 and 6 months after inclusion) will be collected with CastorEDC, (Table 1) and, where applicable, a reminder will be sent after 1 week. Participants will not receive (financial) incentives or other compensation for completion of the questionnaires or the study.

**Table 1 Tab1:** Assessments in the Netherlands (arm A + B) and in Germany (arm C) at baseline and at follow-up of 3 and 6 months

	Baseline assessment (T0)	Follow-up 3 months (T3)	Follow-up 6 months (T6)
Patient characteristics (A + B + C)	X		
Cost questionnaire (A + B)	X	X	X
PAM-13 (A + B + C)	X	X	X
EQ-5D-3 L (A + B + C)	X	X	X
HOOS/KOOS (A + B + C)	X	X	X
SQUASH (A + B + C)	X	X	X
TOA (A + B + C)	X	X	X
IPQ-K (A + B + C)	X	X	X
OA-QI (A + B + C)	X	X	X
SUS (B + C)		X	X
Use of app (B + C)		X	X

*Abbreviations*: *PAM-13*, Patient activation measure, *EQ-5D-3 L* Euro Quality of Life – 5 Dimensions - 3 Level, *HOOS/KOOS* Hip/Knee Osteoarthritis Outcome Score, *SQUASH* Short Questionnaire to assess health-enhancing physical activity, *TOA* Treatment beliefs in knee and hip osteoarthritis, *IPQ-K* Illness Perception Questionnaire, *OA-QI* Osteoarthritis Quality Indicators, *SUS* System Usability Scale

### Study parameters

#### Main study parameter

The main study parameter for the RCT in the Netherlands (arm A vs. B) is the number of self-reported consultations in secondary healthcare (i.e. orthopaedic surgeon, rheumatologist, physician assistant) due to OA in the knee and/or hip in the past 6 months, collected every 3 months. The primary endpoint in the Netherlands is the difference in mean consultations in secondary health care at 6 months between the usual care group (A) and the dr. Bart app group (B).

The primary endpoint for the comparison between the Dutch dr. Bart app group and the German dr. Bart app group (arm B vs. C) is self-management behaviour, as collected with the Patient Activation Measure (PAM-13) questionnaire [52, 53] at 6 months.

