### Sample size

The primary outcome measure for the RCT is number of consultations in secondary health care due to OA of the knee and/or hip in the past 6 months. We performed a sample size calculation for an unpaired t-test to compare two independent means. Based on previous research a mean difference of 0.35 consultations between two independent groups was considered credible, with a standard deviation (SD) of 1.00 [68]. With a power of 0.80 and an alpha (α) of 0.05 (two-sided) a sample size of 129 participants per arm is needed. Accounting for loss to follow-up of 20%, 161 participants per arm will be included. Sample size was calculated with Stata version 13.1.

The second aim of the presented study is to explore cultural differences in use and usability of the app and its effect on clinical outcomes. For pragmatic reasons, we decided to include 161 participants (including 20% loss to follow-up) as well in the German arm of the study (C). A total of 129 participants is sufficient to detect a minimal difference of 4.6 (SD = 13.2) on a 52 point scale in the PAM-13 questionnaire between the Dutch (B) and German (C) groups (all using the dr. Bart app) with a power of 0.80 and an alpha of 0.05 (two-sided). The target sample will be able to detect a small to medium effect size (0.2–0.4) in primary outcomes (i.e. number of consultations in secondary health care and self-management behaviour) between groups.

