### Efficacy

Differences in the primary and secondary outcomes between the two arms of the RCT in the Netherlands (A vs. B) after 3 and 6 months will be assessed by either linear mixed models or Poisson regression, as appropriate, with a random intercept, including treatment group (i.e. usual care (A) or dr. Bart (B)), baseline value and interaction between treatment group and time as covariates. The primary outcome in the Netherlands will be reported as an incidence rate ratio in case of Poisson regression, or negative binomial regression, as appropriate.

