### Economic evaluation from the health care perspective

The economic evaluation is based on the general principles of cost-utility analysis (CUA) and cost-effectiveness analysis (CEA), applying a health care perspective. Direct medical cost in the Netherlands due to OA in the 6 months of follow-up will be analysed, in both primary and secondary care and will be measured retrospectively by online questionnaires on a 3 month recall basis. Standard cost prices of the Dutch costing guideline will be used [54]. To determine the incremental cost-effectiveness ratio (ICER) for the CUA, differences in costs between the usual care group (A) and the dr. Bart group (B) will be divided by differences in QALYs. For the CEA, differences in costs between the groups (A vs. B) will be divided by the differences in secondary outcomes (e.g. physical functioning, physical activity). Uncertainty (95% CI (confidence interval)) around the ICERs will be stochastically determined by the bootstrap method.

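### The recall window of the primary consultation count is stated inconsistently, and the visit-level model does not ensure that the primary test is the 6-month count that was powered

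*Protocol article*

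**What the plan says.** - **Outcome.** Under Main study parameter, the Dutch outcome is self-reported secondary-care consultations "due to OA in the knee and/or hip in the past 6 months, collected every 3 months".
- **Endpoint.** The same section states: "The primary endpoint in the Netherlands is the difference in mean consultations in secondary health care at 6 months", comparing usual care with the app.
- **Sample size.** The Sample size section uses the "number of consultations in secondary health care due to OA of the knee and/or hip in the past 6 months", with a difference of 0.35, SD 1.00, two-sided alpha 0.05 and power 0.80. This gives 129 per arm, or 161 after 20% loss to follow-up. The method is a comparison of single values: "We performed a sample size calculation for an unpaired t-test to compare two independent means".
- **Recall.** Under Economic evaluation, direct medical costs in primary and secondary care over the 6 months of follow-up "will be measured retrospectively by online questionnaires on a 3 month recall basis". The Direct medical costs section builds them from the usage frequency that participants report.
- **Instrument.** Table 1 lists one questionnaire that counts care use, the cost questionnaire, given to arms A and B at baseline, 3 months and 6 months. The protocol does not say outright that it supplies the primary outcome.
- **Analysis.** Under Efficacy, differences "after 3 and 6 months will be assessed by either linear mixed models or Poisson regression, as appropriate, with a random intercept". The other terms are treatment group, baseline value and the treatment-by-time interaction. If a count model is used, "The primary outcome in the Netherlands will be reported as an incidence rate ratio in case of Poisson regression", or from negative binomial regression.

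**The concern.** The primary outcome is a count over a window, so the window is part of its definition. The protocol gives 6 months in two places. If the consultation count comes from the cost questionnaire, it gives 3 months in a third. It adds that a 6-month quantity is collected every 3 months, and does not say whether each report looks back 3 or 6 months or how two reports become one count.

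The efficacy model does not settle this. A random intercept and a treatment-by-time interaction imply one record per visit, whereas the sample size assumes one 6-month count per person. Depending on the recall fielded and the contrast taken, the primary test may address all of the follow-up, its second half, or a window that reaches back before randomisation. In a trial whose researchers are not blinded, that choice should not stay open once data are in.

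**Working it through.** **Inputs.** From Sample size: difference 0.35, SD 1.00, 129 evaluable per arm, two-sided alpha 0.05, power 0.80, 20% loss. My assumptions: a constant effect over the 6 months; correlation rho between the two 3-month counts of 0 to 0.75; no baseline adjustment; normal approximation for two independent means.

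**Formula.** Power = Φ(δ / (s·√(2/n)) − 1.96). With n = 129, √(2/129) = 0.1245.

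**The plan's own figure.** 0.35 / 0.1245 = 2.81; Φ(2.81 − 1.96) = 0.80. Solving for n gives 129 per arm. For dropout, 129 / 0.80 = 161.25 against 161 stated, an immaterial rounding. The figures reproduce for a single 6-month count.

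**Reading 1: 3-month recall, T3 and T6 reports summed.** The sum is the months 0-6 count: δ = 0.35, s = 1.00, power 0.80. An equally weighted average gives the same result, because 0.175 / 0.50 = 0.35 / 1.00.

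**Reading 2: 3-month recall, T6 contrast from the interaction model.** This covers months 3-6 only. With a constant effect, δ = 0.35 / 2 = 0.175. If the 6-month variance is 1.00 and the two halves have equal variance s², then 1.00 = 2s²(1 + rho), so s = √(1 / (2(1 + rho))).

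| rho | s | power at 129 per arm | evaluable n per arm for 80% |
|---|---|---|---|
| 0 | 0.707 | 0.51 | 257 |
| 0.25 | 0.632 | 0.60 | 206 |
| 0.50 | 0.577 | 0.68 | 171 |
| 0.75 | 0.535 | 0.75 | 147 |

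If the whole 0.35 fell in months 3-6, power would be about 0.98 or more at each of these correlations.

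**Reading 3: 6-month recall, T6 contrast.** The T6 report covers months 0-6: δ = 0.35, s = 1.00, power 0.80. This is the powered count.

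**Reading 4: 6-month recall, effect pooled over T3 and T6.** The T3 report covers months −3 to +3. Half of it precedes randomisation and overlaps a 6-month baseline report, and months 0-3 are reported again at T6. The T3 difference is about 0.175, so the average is (0.175 + 0.35) / 2 = 0.2625. With correlation r between the two reports, the SD of the average is √((2 + 2r) / 4). For r = 0.3 it is 0.806 and power is 0.74; for r = 0.9 it is 0.975 and power is 0.58.

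Readings 1 and 3 recover the powered quantity; readings 2 and 4 do not. The text does not choose among them.

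**The case against.** The strongest reply is that a 6-month quantity collected every 3 months simply means a 6-month total gathered in two 3-month instalments. The economic section builds its costs that way, and on this reading the passages agree and summing restores 80% power. If recall is 6 months instead, the endpoint is placed at 6 months, the interaction allows a separate contrast there, and that contrast is the powered count. The 3-month recall is stated for costs, not for the primary outcome, and an analysis plan not shown may settle the rest.

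Much of this stands, and it rules out several stronger conclusions that a reader might draw:

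- *The primary test is not the powered count.* This does not follow, because two of the four readings recover it.
- *Power may be as low as 29%.* That figure (δ = 0.175, SD 1.00) is for a 3-month contrast under 6-month recall, which the protocol does not make the primary endpoint.
- *Costs are double counted.* Under the 3-month recall stated for costs, the T3 and T6 reports adjoin and do not overlap.
- *Reporting a rate ratio is an error.* Planning a count outcome with a t-test and reporting a ratio is common, both address equality of mean counts, and the ratio is conditional on the model. This is largely preference.

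What the reply does not remove is the mismatch inside the document. If the instalments are summed, each person has one value, and a model with a random intercept and a treatment-by-time term does not describe that analysis. If that model is used as written on 3-month reports, its 6-month contrast covers half the follow-up. This concerns what the text says, not detail left for later.

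**Conclusion.** The concern holds in limited form. The recall window of the primary outcome is not stated consistently, and the efficacy model does not ensure a test of the 6-month count that was powered. The consequence depends on which window was fielded:

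- With 3-month recall, the model's 6-month contrast has about 51% to 75% power instead of 80%. This rests on the constant effect, the absence of baseline adjustment and the assumed correlation of 0 to 0.75. Adjusting for baseline, or an effect that builds late, would raise it.
- With 6-month recall, the primary contrast at 6 months is sound, and only the 3-month estimate or a pooled effect is diluted.

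The figures of 129 and 161 per arm need no change. That the cost questionnaire supplies the primary count is inferred from Table 1.

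**What to change.** 1. Reconcile the recall wording under Main study parameter, Sample size and Economic evaluation with the questionnaire actually fielded, and state the look-back at baseline, T3 and T6.
2. Define the primary outcome as one count per participant over months 0-6 after randomisation: the sum of T3 and T6 if recall is 3 months, T6 alone if it is 6 months.
3. Test it with one named count model (negative binomial is already among the protocol's options), adjusted for the baseline count and the hip/knee randomisation stratum.
4. Report the model-based difference in mean consultations, which is the stated endpoint, with the rate ratio alongside. Keep period-specific contrasts as secondary.

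The cost is wording and one model specification before the data are analysed; no new data are needed. One small downside is that, with summed 3-month reports, a participant who misses one needs an offset for months reported or imputation, and the choice should be stated in advance.

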#### Secondary study parameters

Secondary study parameters include direct medical costs, self-management behaviour, health-related quality of life, physical function (in daily living, sport and recreation), physical activity, treatment beliefs in OA, illness perception, perceived quality of care, and use and usability of the dr. Bart app.

### Assessments

#### Direct medical costs

By means of an OA specific questionnaire direct medical costs (i.e. healthcare-related) due to OA in the 6 months of follow-up will be collected, in both secondary and primary healthcare. Standard cost prices of the Dutch costing guideline will be used [54]. Direct medical costs will be computed by multiplying the cost prices with the usage frequency as reported by participants.

#### Self-management behaviour

The PAM-13 questionnaire measures knowledge, skills and confidence to cope with one owns health [55]. The PAM-13 questionnaire is scored on a 13 to 52 scale. A higher score indicates higher level of patient activation. The PAM-13 shows good psychometric capabilities for measuring patient activation [53].

#### Health-related quality of life

EQ-5D-3 L will be used to measure health-related quality of life. This instrument contains questions about; mobility, self-care, usual activities, pain/discomfort and anxiety/depression, scored on a 3-point Likert scale. Moreover, the EQ-5D-VAS (visual analogue scale) will be used to indicate health-related quality of life on a vertical line, ranging from 0 (worst imaginable health) to 100 (best imaginable health) [56, 57].

#### Physical function in daily living, sport and recreation

Pain, symptoms, function in daily living, function in sport and recreation and knee or hip related quality of life in the previous week will be assessed with the Knee or Hip Osteoarthritis Outcome Score (KOOS or HOOS), depending on the affected joint [58, 59]. We will report subscales, since the total score is not validated. A higher score on the subscale indicates less complaints on that domain.

#### Physical activity

Physical activity will be assessed with the Short Questionnaire to Asses Health-enhancing physical activity (SQUASH). The SQUASH is a structured questionnaire consisting of activities at work, commuting, household activities, leisure-time and sports activities [60]. From this questionnaire time spent in light, moderate and vigorous physical activity can be calculated. The SQUASH is considered a reasonably valid tool to assess PA [60, 61].

#### Treatment beliefs in OA

The Treatment beliefs in osteoarthritis (TOA) questionnaire will be used to assess participants beliefs about various treatment modalities in hip and knee OA and is based on the theory of planned behaviour. Both positive and negative beliefs regarding five treatment modalities in OA are assessed; 1) Physical activities, 2) Pain medication, 3) Physical therapy, 4) Injections, 5) Joint replacement surgery. For each subscale items are measured on a 5-point Likert scale (1 ‘disagree to 5 ‘agree’). Psychometric properties are satisfactory to good [62]. The TOA is not yet available in German language. Therefore, we will translate and culturally adapt the TOA to the German language according to the forward and back translation principle [63].

#### Illness perception

Illness perception will be assessed with the brief illness perception questionnaire [64]. This is a short questionnaire consisting of eight dimensions of illness perceptions which can be scored on a 10 point scale. From these eight dimensions a total score can be calculated, where a higher score reflects more threatening views regarding OA than a lower score. An additional open question asks the three perceived most causative factors for an individual’s hip and/or knee OA.

#### Quality of care

A questionnaire regarding quality indicators for OA care is used to assess quality of care [65]. This questionnaire is available in Dutch, but not yet validated. For the German variant, we will translate and culturally adapt the English OA quality indicators questionnaire to the German language according to the forward and back translation principle [63].

#### Usability of the app

The usability of the app will be assessed with the System Usability Scale (SUS) [66, 67]. This questionnaire contains 10 questions regarding usability of the app. A total score ranging from 0 to 100 is calculated, where a higher score indicates better usability. Additionally, we provided a free-text opportunity after each question so that participants could elaborate on their given answers.

#### Adherence to the dr. Bart app

Adherence to the dr. Bart app will be quantitatively measured in the back end of the app. Parameters of use will be logged and extracted automatically for each user:
*The proportion of active users (*e.g. *who completed minimal one goal) over time*
*Number of average logins per active user per week*

*Number of recommended goals, not chosen*

*Number of chosen goals*

*Number of achieved goals*
*Number of goals set to non-active (*i.e. *choose to not do goal anymore)**Number of goals set to active (*i.e. *choose to do goal again)*
*Ranking of goals on the basis of times chosen*

#### Other assessments

Socio-demographic characteristics (i.e. age, gender, length, weight, localization and duration of OA symptoms, marital status, living situation, education, ethnicity, and (paid) work) will be collected at baseline.

### Sample size

The primary outcome measure for the RCT is number of consultations in secondary health care due to OA of the knee and/or hip in the past 6 months. We performed a sample size calculation for an unpaired t-test to compare two independent means. Based on previous research a mean difference of 0.35 consultations between two independent groups was considered credible, with a standard deviation (SD) of 1.00 [68]. With a power of 0.80 and an alpha (α) of 0.05 (two-sided) a sample size of 129 participants per arm is needed. Accounting for loss to follow-up of 20%, 161 participants per arm will be included. Sample size was calculated with Stata version 13.1.

The second aim of the presented study is to explore cultural differences in use and usability of the app and its effect on clinical outcomes. For pragmatic reasons, we decided to include 161 participants (including 20% loss to follow-up) as well in the German arm of the study (C). A total of 129 participants is sufficient to detect a minimal difference of 4.6 (SD = 13.2) on a 52 point scale in the PAM-13 questionnaire between the Dutch (B) and German (C) groups (all using the dr. Bart app) with a power of 0.80 and an alpha of 0.05 (two-sided). The target sample will be able to detect a small to medium effect size (0.2–0.4) in primary outcomes (i.e. number of consultations in secondary health care and self-management behaviour) between groups.

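### The claimed detectable range of 0.2–0.4 SD is not supported: the trial is sized for 0.35 SD, and power at 0.2 is about 36%

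*Protocol article*

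**What the plan says.** All the relevant text is in the Sample size section of the protocol article.

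- **Dutch randomised comparison (A vs B).** The method is given as "We performed a sample size calculation for an unpaired t-test to compare two independent means". The inputs are that "a mean difference of 0.35 consultations between two independent groups was considered credible", "with a standard deviation (SD) of 1.00 [68". The result is "With a power of 0.80 and an alpha (α) of 0.05 (two-sided) a sample size of 129 participants per arm is needed", raised to 161 enrolled for 20% attrition.
- **Dutch–German comparison (B vs C).** The German arm is set at 161 for practical reasons. The plan says 129 suffices for a PAM-13 difference of 4.6 points with SD 13.2, at the same power and alpha, and describes that as the smallest difference detectable.
- **Closing sentence.** "The target sample will be able to detect a small to medium effect size (0.2–0.4) in primary outcomes", with secondary-care consultations and self-management behaviour both named as the outcomes meant.

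No separate calculation, power level or alpha is given for the 0.2 end of the range.

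**The concern.** Both calculations rest on a standardised difference of about 0.35. A sample that has just 80% power at 0.35 cannot have comparable power at 0.2, because the required sample size grows with the inverse square of the effect. The closing sentence therefore credits the design with a sensitivity it lacks. It also conflicts with the same paragraph, where about 0.35 SD is the smallest PAM-13 difference 129 can detect.

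What is at stake is how a null result is read. In a statement of detectable effects the lower bound is the informative part. If the trial finds no significant difference, a reader relying on this sentence could conclude that an effect of 0.2 SD had been looked for adequately and not found. Small effects are plausible on the plan's own account: the Background reports only small benefits from conventional self-management programmes in osteoarthritis, although on outcomes other than consultations.

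**Working it through.** **Inputs, from the Sample size section unless noted**

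- Two-sided alpha 0.05, power 0.80, unpaired t-test
- A vs B: difference 0.35, SD 1.00, so d = 0.35
- B vs C: difference 4.6, SD 13.2, so d = 4.6/13.2 = 0.348
- 129 analysed per arm, 161 enrolled per arm
- "allocation ratio 1:1" for A vs B (Randomization, allocation concealment and blinding)

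**Step 1. Reproduce the plan's figures**

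Normal approximation: n per arm = 2(z₀.₉₇₅ + z₀.₈₀)²/d², with (1.960 + 0.842)² = 7.849.

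- A vs B: 2 × 7.849/0.35² = 128.1, rounded up to 129. The noncentral t solution is 129.1.
- B vs C: 2 × 7.849/0.348² ≈ 129.3, rounded up to 130. The noncentral t solution is 130.2. The plan's 129, read as per group, gives 79.6% power, so it agrees for practical purposes.
- Attrition: 129/(1 − 0.20) = 161.25, against 161 stated.

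The stated sample sizes reproduce, so the method used here matches the plan's.

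**Step 2. Smallest difference detectable with 80% power**

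d = (1.960 + 0.842) × √(2/n).

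- n = 129: 2.802 × 0.1245 = 0.349 (noncentral t: 0.350)
- n = 161: 2.802 × 0.1115 = 0.312 (noncentral t: 0.313)

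**Step 3. Power across the claimed range**

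Power ≈ Φ(d/√(2/n) − 1.960). For d = 0.2 and n = 129: 0.2/0.1245 = 1.606, and Φ(−0.354) ≈ 0.362. The table gives noncentral t values.

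| d | 129 per arm | 161 per arm |
|---|---|---|
| 0.20 | 36% | 43% |
| 0.25 | 52% | 61% |
| 0.30 | 67% | 77% |
| 0.35 | 80% | 88% |
| 0.40 | 89% | 95% |

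**Step 4. What 0.2 would require**

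2 × 7.849/0.2² = 392.4, rounded up to 393; the noncentral t solution is 393.4, so 394 analysed per arm. With 20% attrition that is 394/0.8 = 492.5, or 493 enrolled per arm, about three times the plan.

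**Step 5. What a null result would look like**

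The 95% confidence interval half-width is 1.960 × √(2/n): about 0.24 SD with 129 per arm and 0.22 SD with 161. Even an estimate of exactly zero would leave 0.2 SD inside the interval.

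**Step 6. Can another reading rescue 0.2?**

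- *No attrition:* power is 43%.
- *One-sided 0.05, which the plan does not use:* 48% with 129 per arm, 56% with 161.
- *Baseline adjustment (Efficacy section):* if variance falls by the factor 1 − ρ², 80% power at 0.2 needs ρ = √(1 − (0.2/0.349)²) = 0.82 with 129 per arm, or 0.77 with 161. The plan states no such correlation, and its calculation is unadjusted.

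**The case against.** The strongest reply is that the sentence drives nothing. Enrolment comes from the explicit calculation, which is right. No threshold, decision rule or analysis uses 0.2, and the correct differences, SDs, power and alpha are in the same section for anyone to see. The sentence attaches no power level to its range, so 0.2–0.4 may have been meant only as a verbal band containing 0.35. The Dutch–German comparison is described as exploratory, and the plan does not say it will read a null result against 0.2. Part of the band, 0.35 to 0.4, is supported.

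Much of this stands as a limit on consequences. Correcting the sentence changes neither enrolment nor analysis, and the misreading of a null result is a risk rather than something the plan commits to. The power loss is also graded: the trial would miss a true 0.2 more often than not, detection at 0.25 is about even, and at 0.3 it is about two in three with 129 per arm.

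It does not make the sentence true. It is worded as a statement of what the sample can detect, follows directly on two 80% power calculations, and gives no other criterion.

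Two further points affect only the wording of the correction. The target sample could be taken as 161 rather than 129, so both sets of figures should be given; 129 is the plan's own analysed number after attrition. The planned models are baseline-adjusted mixed models or count regressions, so the corrected figures should be tied to the unadjusted t-test used for sizing.

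**Conclusion.** The concern holds. The plan claims sensitivity down to 0.2 SD in both primary outcomes, but its own inputs give 80% power only from about 0.35 SD with 129 analysed per arm, or 0.31 SD with all 161. A true effect of 0.2 SD (0.2 consultations at SD 1.00, or 0.2 × 13.2 = 2.6 PAM-13 points) would be missed about 64% of the time with 129 per arm and 57% with 161.

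These figures assume the plan's unpaired t-test, its SDs, equal arms and two-sided alpha 0.05. They do not describe the power of the mixed or count models that may be fitted. The sample size and the upper part of the range are sound. The error is a misstated design property and bears on interpretation, not on conduct.

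**What to change.** Replace the closing sentence of the Sample size section with, for example:

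*Under the unadjusted two-sided t-test used for sizing, with 129 analysed per arm the smallest standardised difference detectable with 80% power is 0.35 (0.31 if all 161 per arm are analysed); power for a difference of 0.2 is about 36% (43% with 161).*

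Add that a non-significant primary result will be interpreted from its confidence interval and not as evidence against effects smaller than this.

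The cost is one or two sentences and a less favourable statement of sensitivity. No patients are added, and no endpoint or analysis changes. Keeping 0.2 as a real target would instead need about 394 analysed, or 493 enrolled, per arm.
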